### Retrospective cohort study

We have previously reported that more than half of the HCA are discovered after the patient has sustained at least one pregnancy and none of these patients have reported problems during their pregnancies 
[19]. As mentioned above, recently we described a small but unique series of 12 women with documented HCA who were closely monitored during a total of 17 pregnancies between 2000 and 2009. In 4 cases HCA’s grew during pregnancy, requiring a Caesarean section in 1 patient (2 pregnancies) and RFA in 1 case during the first trimester of pregnancy to treat a hormone sensitive HCA, thereby excluding potential growth later on in pregnancy. No intervention was performed in the other 14 cases. All pregnancies had an uneventful course with a successful maternal and fetal outcome and we concluded that a “wait and see” management may be advocated in pregnant women presenting with HCA. In women with large tumours or in whom HCA had complicated previous pregnancies, surgical resection may be recommend 
[21]. However, additional data from different centres for the risk of hormone induces growth and rupture of HCA during pregnancy is needed.

### Interventions

During their pregnancy HCA patients will be closely monitored by means of repetitive US (and MRI in case of growth of the lesion) at 14 (+/−3) and 20 and 26 and 32 and 38 weeks of gestation and 6 and 12 weeks postpartum. At the same days both control groups will be asked to fill out the SF-12 and EQ-5d questionnaire at 14 (+/−3) and 20 and 26 and 32 and 38 weeks of gestation and at 6 and 12 weeks postpartum (Fig. 1). The study group will be asked to fill out the SF-12, EQ-5d, STAI-6 and IES questionnaires before and one week after US of the HCA lesion(s). Both control groups will undergo US of the liver at 14 (+/−3) weeks of gestation to exclude HCA lesions in the liver. At 14 and 32 weeks of pregnancy all patient groups will undergo venapunction.

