## Methods/design

### Study objective

In this study we will investigate the management and outcome of HCA during pregnancy and labor based on a prospectively acquired online database in the Netherlands.

Main objective of the PALM-study

 • To investigate the incidence of HCA growth during pregnancy and labor.

Secondary objectives of the PALM-study

 • To investigate in which trimester of pregnancy growth of HCA occurs;

 • To investigate the degree of growth of HCA during pregnancy;

 • To investigate whether there is regression of HCA postpartum;

 • To investigate the HCA-related interventions during pregnancy and labor;

 • To investigate the incidence of bleeding of HCA during pregnancy and labor;

 • To investigate liver-related clinical signs during pregnancy;

 • To investigate elevated liver enzymes during pregnancy;

 • To evaluate the health related quality of life of pregnant patients with HCA;

 • To investigate whether there is a difference between health related quality of life of pregnant patients with HCA and pregnant patients with other comorbidity that have an indication for pregnancy care at the obstetrician in secondary care and healthy pregnant patients.

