### Study design

The PALM-study is a multi-centre prospective study in three cohorts of pregnant women. The study started on November 1 2011 and inclusion of patients will be a period of minimal 3 to maximal 5 years. In total 50 pregnant patients with HCA < 5 cm will be included in the study. These patients will be compared to a healthy control group consisting of 63 pregnant patients without HCA and a group consisting of 63 pregnant patients with diabetes mellitus (DM). Approval of the Medical Ethics Committee of Erasmus Medical Centre was obtained, NL36058.078.11.

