### Outcome measures

Primary outcome: Biological behaviour and clinical consequences of HCA < 5 cm during pregnancy. Growth is measured by repetitive US (and MRI in case of growth) at 14 (+/−3) and 20 and 26 and 32 and 38 weeks of gestation.

Secondary outcome: General health and pain scales as a measure for quality of life and anxiety related questionnaires for thoughts and feelings of adenomas around US. Other secondary outcomes are complications due to growth of the HCA during pregnancy possibly followed by interventions during pregnancy, incidence of hemorrhage and rupture of the HCA, incidence of liver-related clinical signs during pregnancy (itch, icterus), incidence of elevated liver enzymes during pregnancy.

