## Discussion

Once the diagnosis of HCA has been established, patients will be advised to discontinue OC. Expert opinions are very variable regarding treatment and follow up in complex situations were multiple factors play a role in determining the management strategy, like pregnancy 
[18].

As to date there are limited data about the behavior of HCA during pregnancy and labor and therefore we cannot identify precisely those at risk for complications. However, in 2006 we reported a series of 48 patients of which in 44% HCA were discovered after the patient had sustained at least one pregnancy 
[19]. None of these patients have reported problems during their pregnancies. Likely, only a small subgroup of patients may experience complications and to date pregnancy might be discouraged in too many patients caused by unnecessary intervention before pregnancy. We hypothesize that pregnancy may be allowed in case of one or more known HCA < 5 cm (without previous intervention), because HCA < 5 cm will not disturb the course of pregnancy. Close monitoring during pregnancy by means of repetitive US (and MRI in case of growth) should be carried out to rule out rapid growth of the lesion. The risk of rupture seems the highest during the third trimester of pregnancy 
[20]. Most likely due to the cumulating level of estrogens and an increase in hyperdynamic circulation combined with an increase in vascularity of the liver with growth of the adenoma 
[20]. Symptoms and the level of liver enzymes will be registered to find out if there is a relation between symptoms, elevated liver enzymes and growth of the HCA during pregnancy. Patients will be followed-up postpartum to investigate if there is a risk of HCA complications after delivery.

The Society of American Gastrointestinal and Endoscopic Surgeons (SAGES) provided guidelines for diagnosis, treatment, and use of laparoscopy for surgical problems during pregnancy 
[26]. However, these guidelines are mostly based on case reports and retrospective studies and therefore graded at a low level of evidence. The SAGES suggest that MRI without the use of intraveneous gadolinium, and US is considered safe and can be used at any stage of pregnancy (Level IIIB and Level IIA respectively) 
[26]. Data regarding safety of CEUS during pregnancy is scare and yet uncertain. However, Hua et al. reported an animal study in which SonoVue may affect the placenta 

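### Blood drawn only at 14 and 32 weeks gives elevated liver enzymes at two visits, at best a lower bound on the stated incidence during pregnancy, and leaves growth first seen at 38 weeks without an enzyme value

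*Protocol article*

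**What the plan says.** The blood schedule is in the protocol article under Interventions: "At 14 and 32 weeks of pregnancy all patient groups will undergo venapunction". The Patient selection paragraphs for the study group and both control groups agree with it, and so does Table 1. No blood is scheduled at 20, 26 or 38 weeks.

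Three statements depend on those samples:

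- Study objective lists a secondary objective: "To investigate elevated liver enzymes during pregnancy".
- Outcome measures lists among the secondary outcomes the "incidence of elevated liver enzymes during pregnancy".
- The Discussion says symptoms and enzyme levels will be recorded "to find out if there is a relation between symptoms, elevated liver enzymes and growth of the HCA during pregnancy".

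Growth has a denser schedule. Outcome measures states: "Growth is measured by repetitive US (and MRI in case of growth"), with scans in the adenoma group at 14 (±3), 20, 26, 32 and 38 weeks. The scan at 14 weeks is the baseline. The Discussion also remarks: "The risk of rupture seems the highest during the third trimester of pregnancy".

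**The concern.** An incidence during pregnancy counts women in whom an elevation occurs at any time in that period. Two samples 18 weeks apart record status at two moments. A rise that comes and goes between them, or that begins after the second, leaves no trace in the scheduled data.

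The planned relation with growth has a similar gap. Growth can first be declared at a scan with no blood drawn, and at 38 weeks no scheduled sample is taken then or later. If the trial found no relation, part of the reason could be that enzymes were not measured when late growth appeared. Taken as a finding about the whole pregnancy, such a null would claim more than the samples can show. A later analysis plan cannot repair this, because it cannot supply samples that were never taken.

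**Working it through.** The document gives no figure for liver enzymes, so there is none to reproduce. The check sets the two schedules side by side and then asks how much the gaps could matter.

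**1. Scan and blood schedules in the adenoma group (Interventions, Table 1)**

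| Week | Scan | Blood | Scheduled enzyme value for growth first seen here |
|---|---|---|---|
| 14 (±3) | yes (baseline) | yes | reference value |
| 20 | yes | no | next sample 32 − 20 = 12 weeks later |
| 26 | yes | no | next sample 32 − 26 = 6 weeks later |
| 32 | yes | yes | same visit |
| 38 | yes | no | none at or after |

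Of the four scans that can show growth from the week-14 baseline, one (week 32) has blood at the same visit. Three (20, 26 and 32) have a sample at or after them. Only week 38 has neither. The Online database section also records lesion size before pregnancy, so growth by week 14 against that size could be paired with the first sample.

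**2. What the two samples estimate**

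- The proportion elevated at week 14 and the proportion elevated at week 32.
- New elevation at week 32 among women normal at week 14.
- The proportion elevated at either visit. It cannot exceed the proportion ever elevated in pregnancy, so it is a lower bound. An elevation already present at week 14 may also predate the pregnancy, so the first sample alone does not show new onset.

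**3. Size of the gap, under stated assumptions**

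The document gives neither the onset nor the duration of enzyme rises. Assume onset is uniform between weeks 14 and 40, a span of 40 − 14 = 26 weeks, and that each rise lasts d weeks. The week-32 sample catches a rise that starts between weeks 32 − d and 32. For d up to 18 the share caught is d/26. For rises that persist to delivery it is (32 − 14)/26.

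| Duration | Share caught at week 32 |
|---|---|
| 2 weeks | 2/26 = 7.7% |
| 4 weeks | 4/26 = 15.4% |
| 8 weeks | 8/26 = 30.8% |
| 12 weeks | 12/26 = 46.2% |
| persistent | 18/26 = 69.2% |

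Rises that start after week 32 make up (40 − 32)/26 = 8/26 = 30.8%, and the schedule misses them whatever their duration. The model leaves out elevations already present at week 14, which the first sample would detect.

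**4. Numbers available for the growth relation**

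The Power calculation section cites growth in 24% of earlier pregnancies. With 50 women in the adenoma group, that is 0.24 × 50 = 12 with growth. The document does not say how many of these would be first seen at 38 weeks, so the number falling outside the sampled window is unknown.

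**The case against.** The strongest reply is that the schedule supports a good deal. Prevalence at two visits and new elevation by week 32 are estimable, and enzyme change can be set against lesion change over the same 18 weeks. All three groups share the schedule, so any comparison of enzymes at the two visits remains fair. The outcome is secondary, no power is claimed for it, and the relation with growth rests on one sentence in the Discussion. All of this stands.

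Several stronger readings are tempting, and the documents do not support them:

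- **That incidence cannot be addressed at all.** The samples give a lower bound and a valid analysis from 14 to 32 weeks.
- **That only one scan in four is covered.** This is true for blood at the same visit, but growth first seen at 20, 26 or 32 weeks does have a sample at or after it. Only week 38 has none.
- **That the undercount is known to be large.** It depends on duration and onset, which the documents do not give. Quoting only short durations would hide the 46% and 69% cases. The article also does not limit enzyme recording to the two visits, and the handling of unscheduled results may be in the full protocol.
- **That extra tests will bias the comparison against controls.** Nothing says unscheduled results will be pooled with scheduled ones. The diabetes group is also under the obstetrician, and healthy women with complications are referred there.
- **That a null result will drive the decision-making model.** No text says enzymes enter it. The Hypothesis section defines a disrupted pregnancy by interventions and by quality of life or anxiety.
- **That the remark on the third trimester shows enzymes rise then.** It concerns rupture, and week 32 itself lies in the third trimester.

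The mismatch between the named outcome and the scheduled samples remains after all of this.

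**Conclusion.** The point holds as a minor one on a secondary outcome. The scheduled data support proportions elevated at 14 and 32 weeks and new elevation by week 32, which is at best a lower bound on incidence over the whole pregnancy. Growth first seen at 38 weeks has no enzyme value at that visit or later, so a null enzyme-growth relation would be weak evidence for late pregnancy.

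The size of the shortfall is not known. The illustrative range of about 8% to 69% caught rests wholly on uniform onset over weeks 14 to 40 and on assumed durations from 2 weeks to persistent. It should not be read as an estimate for this trial. The conclusion itself needs only the two schedules.

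The primary growth outcome and the quality-of-life comparison do not depend on these samples and are unaffected.

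**What to change.** - **Outcome measures:** replace the incidence wording with the proportion of women with elevated liver enzymes at 14 weeks and at 32 weeks, plus new elevation at 32 weeks among those normal at 14. Base these on scheduled samples and report any unscheduled tests separately.
- **Discussion:** limit the enzyme-growth analysis to change in enzymes against change in lesion size from 14 to 32 weeks. State that growth first seen at 38 weeks is outside it, and that no conclusion about enzymes and late growth will be drawn.
- **Study objective:** this does not use the word incidence, so it needs only to be read consistently with the revised outcome.

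The cost is a few lines of text and no extra blood. The downside is a narrower claim than incidence over the whole pregnancy.

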### Online database

We established a website which allows hepatologists, surgeons and gyneacologists to submit clinical data in an online database. Each centre will have a code to log in and patients will be consecutively assessed a unique number. Registration of a new patient includes entry of the following data: date of birth, weight, height, date of hospital admission, symptoms at presentation, known risk factors for HCA such as glycogenosis and familial polyposis, 
[24] previous pregnancies, previous use of OC or other hormone medication including hormone replacement therapy, course of HCA after discontinuation of OC, size of HCA before pregnancy, size of HCA during pregnancy (14 (+/−3) and 20 and 26 and 32 and 38 weeks), course of HCA postpartum (6 and 12 weeks postpartum), complications and management during pregnancy, gestation time, way of delivery (vaginally, Caesarean section), maternal and fetal outcome, complications and management after delivery. Only authorized users can gain action to the online database of his or her patients. The database offers excess to the registered data on anytime and anywhere. The coordinating investigator will monitor whether all required fields are completed.

### Follow-up

Follow-up of patients takes place at 6 and 12 weeks postpartum postpartum by means of US (and MRI in case of growth) to document the size of HCA postpartum (Table 
1). Both control groups will be asked to fill out the SF-12 and EQ-5d questionnaires at these days. The study group will be asked to fill out the SF-12, EQ-5d, STAI-6 and IES questionnaires before and one week after US of the HCA lesion(s).

**Table 1 T1:** Follow-up PALM-study

**Pregnancy**			
**Weeks**	**Ultrasonography**	**Venapunction**	**Questionnaires**
14	S, C1, C2	S, C1, C2	S, C1, C2 *
20	S		S, C1, C2 *
26	S		S, C1, C2 *
32	S	S, C1, C2	S, C1, C2 *
38	S		S, C1, C2 *
**Post-partum**			
**Weeks**	**Ultrasonography**	**Venapunction**	**Questionnaires**
6	S		S, C1, C2 *
12	S		S, C1, C2 *

S, study group; C1 control group 1 (healthy pregnant patients without HCA); C2, control group 2 (pregnant patients with Diabetes Mellitus).

*The study group will be asked to fill out the SF-12, EQ-5d, STAI-6 and IES questionnaires before and one week after US of the HCA lesion(s). Both control groups will be asked to fill out the SF-12 and EQ-5d questionnaire.

### Outcome measures

Primary outcome: Biological behaviour and clinical consequences of HCA < 5 cm during pregnancy. Growth is measured by repetitive US (and MRI in case of growth) at 14 (+/−3) and 20 and 26 and 32 and 38 weeks of gestation.

Secondary outcome: General health and pain scales as a measure for quality of life and anxiety related questionnaires for thoughts and feelings of adenomas around US. Other secondary outcomes are complications due to growth of the HCA during pregnancy possibly followed by interventions during pregnancy, incidence of hemorrhage and rupture of the HCA, incidence of liver-related clinical signs during pregnancy (itch, icterus), incidence of elevated liver enzymes during pregnancy.

### Power calculation

In our previous study we measured growth of HCA in 4 out of 17 pregnancies (24%) or in 3 out of 12 women (25%). On a yearly basis approximately 50 new patients with HCA are seen at the outpatient clinic of the Erasmus University Medical Centre. The expectation is that 5% (5) of these women get pregnant. The expectation is that a total of 50 pregnant HCA patients from different tertiary referral centres in the Netherlands can be included in the study during a period of 3 to maximum 5 years.

A difference of 0.5 Cohen’s D in health-related quality of life is a relevant difference 
[25]. We calculated that for this purpose 63 patients in both control groups have to be enrolled. A two-sample *t* test was performed with a two-sided significant level of 0.05 and a power of 0.80.

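### The 63 controls per group is an equal-group sample size; with the HCA group fixed at 50, each quality-of-life comparison has about 74% power, not the stated 80%

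*Protocol article*

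**What the plan says.** The Power calculation section sets the target difference: "A difference of 0.5 Cohen’s D in health-related quality of life is a relevant difference". It gives the resulting size of the control groups, "We calculated that for this purpose 63 patients in both control groups have to be enrolled", and the basis: a two-sample t "test was performed with a two-sided significant level of 0.05 and a power of 0.80".

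The size of the HCA group has a different origin. The same section derives it from expected recruitment over three to five years: "The expectation is that a total of 50 pregnant HCA patients from different tertiary referral centres in the Netherlands can be included in the study". The Study design section repeats the number, "In total 50 pregnant patients with HCA < 5 cm will be included in the study", and sets out the comparison: "These patients will be compared to a healthy control group consisting of 63 pregnant patients without HCA and a group consisting of 63 pregnant patients", the latter having diabetes mellitus. The Abstract gives the same three group sizes.

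The Study objective section lists the comparison among the secondary objectives: "To investigate whether there is a difference between health related quality of life of pregnant patients with HCA and pregnant patients with other comorbidity", and also with healthy pregnant women. The main objective is the incidence of HCA growth.

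**The concern.** The power statement depends on two group sizes, and only one of them is in the calculation. The figure of 63 is the textbook answer for two groups of equal size. The group that enters both comparisons has 50. The only pair in the study that is 63 against 63 is healthy against diabetic controls, and the objectives do not ask for that contrast.

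Two features make this worth correcting although the outcome is secondary. This is the only power calculation in the article, and it is the sole stated basis for enrolling 126 control women. In addition, the Hypothesis section counts decreased quality of life as part of a disrupted course of pregnancy, while the hypothesis is that HCA below 5 cm does not disturb pregnancy. A missed deficit would thus favour the hypothesis, and readers would judge a null result by a power that the design does not have.

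**Working it through.** **Inputs, all from the article.** d = 0.5, two-sided alpha 0.05, power 0.80, two-sample t test, 63 per control group (Power calculation); 50 HCA patients (Abstract, Study design, Power calculation); HCA compared with healthy and with diabetic controls (Study objective, Study design).

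**Step 1: reproduce the plan's figure.** With equal groups and the normal approximation,

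n per group = 2 × (1.96 + 0.8416)² / 0.5² = 62.8, rounded up to 63.

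The exact t calculation gives 63.8, that is 64. Power at 63 against 63 is 80.1% (normal) or 79.5% (t). The 63 is therefore reproduced, with equal allocation.

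**Step 2: enter the planned HCA group.** The noncentrality is d / √(1/n₁ + 1/n₂).

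- 63 against 63: 0.5 / √(1/63 + 1/63) = 2.806
- 50 against 63: 0.5 / √(1/50 + 1/63) = 2.640

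At 50 against 63, the normal approximation gives Φ(2.640 − 1.960) = 75.2%. The noncentral t with 50 + 63 − 2 = 111 degrees of freedom gives 74.4%.

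**Step 3: what the design can detect.** With 50 against 63 and 80% power, the detectable difference is (1.96 + 0.8416) × √(1/50 + 1/63) = 0.531 (normal), or 0.535 (t).

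**Step 4: what 80% power at d = 0.5 would require.** With 50 HCA patients, each control group would need 85 women (normal) or 88 (t; power 80.05%).

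**Step 5: could another reading give 80%?**

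| Reading | Power at d = 0.5 (t) | In the article? |
|---|---|---|
| 50 vs 63, two-sided | 74.4% | Yes, as planned |
| 50 vs 63, one-sided 0.05 | 83.6% | No, the text says two-sided |
| 50 vs 126, controls pooled | 84.5% | No, pooling is not described, and 63 per group does not follow from it |
| 63 vs 63 | 79.5% | Only control against control, which is not an objective |

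**Step 6: illustration of loss.** The article gives no dropout rate, so these are assumptions. If 10% of women are lost entirely (45 against 57), power is 70.0%. With 20% (40 against 50) it is 64.5%.

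**The case against.** The arithmetic is hard to contest: no redaction, table damage or condensation for a journal explains it, because inputs, result and power are all printed. The case on the other side is about weight, and much of it stands.

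- *The outcome is secondary.* The main objective, the incidence of HCA growth, is untouched. Power falls by 5 to 6 points and the detectable difference moves from 0.50 to about 0.535. This stands, and it keeps the point below the level of a design failure.
- *The 50 is a feasibility number.* The HCA group cannot readily be enlarged. This also stands; it is why the remedy is to restate the power.

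Two stronger inferences are tempting and are not supported.

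A reader might infer that the trial will analyse quality of life with a single t test and that this should be replaced. The t test is named only as the basis of the sample-size calculation. The analysis method is not given in the article, and an analysis plan that is not shown may already use all rounds.

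A reader might also infer that a repeated-measures model over the seven questionnaire rounds would restore the power. Under equal correlation rho between rounds, the variance of a woman's mean is multiplied by (1 + 6·rho)/7. For 50 against 63 with no loss and the same 0.5 SD effect at every round, this gives 93% power at rho = 0.5, 82% at rho = 0.8 and 78% at rho = 0.9. At rho = 0.8 with 10% loss of women it is also 78%, and with 20% loss 73%. The article gives no rho, so a return to 80% cannot be promised. Such a model also changes the target to an average over pregnancy and the postpartum period.

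**Conclusion.** The stated power is wrong as written. The figure of 63 per control group belongs to an equal-group design, and the planned comparisons are 50 against 63. Each has about 74% power at d = 0.5 (75% by the normal approximation), or 80% power at d of about 0.54. The chance of missing a true 0.5 SD deficit is about 26%, not 20%.

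This assumes full enrolment, no loss, equal variances, and each control comparison tested at two-sided 0.05, as the article's calculation implies. It should be fixed, but it is a modest shortfall on a secondary outcome. It does not show that the study is too small for its main objective or that more women must be enrolled.

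**What to change.** Restate the result in the Power calculation section along these lines: 50 HCA patients against 63 controls per group give about 74% power for d = 0.5, or 80% power for d of about 0.54, before any loss to follow-up. Interpret a null quality-of-life result against that figure. If loss scenarios are added, label them as assumptions.

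The cost is one or two sentences and a less favourable stated power. No extra enrolment is needed; about 88 controls per group would be the price of keeping 80% at d = 0.5.

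Optional: if the analysis plan does not already do so, use the seven scheduled SF-12 and EQ-5D rounds in a repeated-measures model. State that the target is then an average over pregnancy and postpartum, and that any gain depends on the within-woman correlation, on an effect similar across rounds and on little loss. Do not quote a recovered power.
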